### Inclusion criteria for the data extraction from CPRD

School-aged children with asthma aged between 4 and 16 years old as of 1 September 2021 with a coded diagnosis of asthma who have been prescribed asthma medication in the last 12 months were included.

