**Methods/design:**

The TRAINS study—TRial to Assess Implementation of New research in a primary care Setting—is a pragmatic cluster randomised implementation trial using routine data. A total of 1389 general practitioner (GP) practices in England will be included into the trial; 694 GP practices will be randomised to the intervention group and 695 control group of usual care. The Clinical Practice Research Datalink (CPRD) will send the intervention and obtain all data for the study, including prescription and primary care contacts data. The intervention will be sent in June 2021 by postal and email to the asthma lead and/or practice manager. The intervention is a letter to GPs informing them of the PLEASANT study findings with recommendations. It will come with an information leaflet about PLEASANT and a suggested reminder letter and SMS text template.

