### Primary research aim

The aim of this trial is to assess if informing GP practices about the findings of PLEASANT increases prescription uptake in school-age children with asthma. The primary objective of the trial is to determine whether the intervention increases asthma prescription uptake in children with asthma in August and September.

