### The intervention

Selected GP practices currently registered with CPRD and randomised to the intervention arm will receive correspondence twice, once by email and once by mail. The intervention is a letter that highlights the drop in prescription uptake for children with asthma during the summer holidays and introduces the results of the PLEASANT trial. In addition, it advises GP practices on the effect of reminding parents of children with asthma to continue taking their asthma preventer medications during the summer holidays. It will be sent with the assistance of the CPRD to the CPRD contact lead at GPs along with the named to the practice manager and asthma lead. The plan, subject to confirmation and amendment, is that the intervention will be sent by July 2021, which is the advice from the trial steering committee (TSC). Given the timing of the intervention, the hope is that GP practices will then send their correspondence to parents during the school holidays. It is hoped the intervention can be timed to enable sufficient time for GP practices to implement the advice from the intervention.

As this is an implementation study, the correspondence to GP practices is advisory, and the decision on implementation is down to the individual GP practices.

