### Primary outcome measure

The proportion of children with asthma who have a prescription for an asthma preventer medication from 1 August 2021 to 30 September 2021.

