### Data source

The data for this study will be routinely collected data extracted from the Clinical Practice Research Datalink—Aurum (CPRD Aurum) database. This database covers approximately 20% of the UK’s population, with over 1300 general practices participating [16]. CPRD Aurum is a database of de-identified patient data that can capture all medical contacts, from prescription requests to out-of-hours contacts, along with the reason for the contact. The data is contributed by general practices.

CPRD will extract data from primary care medical 6 months post-follow-up. The research team will receive all data fully anonymised and will not have access to any patient identifiable data.

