### Statistics

#### Sample size

The sample size is based on feasibility and the anticipated number of practices providing data to the CPRD. We anticipate a sample size of approximately 1389 GP practices (694 on intervention and 695 on control). Alongside this, from the previous study (PLEASANT), we also anticipate 85 school-age children having asthma per practice [14]. Assuming an expected rate of 30% of people collecting their prescription and an intraclass correlation of 0.03, it is anticipated that the precision of the estimates in the study—estimated as a half-width of a 95% confidence interval—will be 1%.

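### The 12-month prescription look-back that decides which children are analysed has no end date, and both dates the article offers run it past dispatch of the letter and into the primary outcome window

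*Protocol article*

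**What the plan says.** The section on inclusion criteria for data extraction takes children aged 4 to 16 "as of 1 September 2021 with a coded diagnosis of asthma who have been prescribed asthma medication in the last 12 months". No other section dates the 12 months.

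The primary outcome is the proportion of children "who have a prescription for an asthma preventer medication from 1 August 2021 to 30 September 2021".

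Dispatch is dated three ways. The abstract says "The intervention will be sent in June 2021 by postal and email". The intervention section says "the intervention will be sent by July 2021". The list of secondary outcomes counts six months from 1 July 2021.

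On extraction, the data source section says "CPRD will extract data from primary care medical 6 months post-follow-up", and the trial design section describes extraction over six months after implementation. The primary objective is to "determine whether the intervention increases asthma prescription uptake in children with asthma in August and September".

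The analysis is by intention to treat. The primary model adjusts for age, sex and the number of preventer prescriptions in the baseline period (August and September of 2019 and 2020), with practice as a random effect.

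**The concern.** Randomisation protects the comparison only if arm cannot affect who is counted. Here a recent asthma prescription makes a child eligible, a preventer prescription is the outcome, and the letter is meant to raise prescribing. If the look-back extends beyond dispatch, the letter can act on eligibility as well as on the outcome.

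Take a child with no asthma prescription in the part of the look-back before dispatch.

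- If the child is given a preventer in August 2021, the child enters the denominator and counts as a success.
- If the child is given only a reliever in July or August, and no preventer by 30 September, the child enters as a failure.
- If nothing is prescribed, the child is absent rather than a failure.

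If the letter makes the first two events more common in one arm, the arms contain different kinds of children, and the primary estimate mixes the effect on uptake with a change in who is counted.

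**Working it through.** **1. The plan's own precision.** The sample size section gives 694 and 695 practices, 85 children per practice, 30% uptake and an intraclass correlation of 0.03.

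- Design effect = 1 + (85 - 1) × 0.03 = 3.52.
- Children per arm: 694 × 85 = 58,990 and 695 × 85 = 59,075.
- Half-width of the difference = 1.96 × sqrt(0.30 × 0.70 × 3.52 × (1/58,990 + 1/59,075)) = 0.98 points. The stated 1% is reproduced.

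**2. Overlap if the look-back ends at 1 September 2021.**

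- The outcome window, 1 August to 30 September, has 61 days. August supplies 31 of them: 31/61 = 50.8%.
- Days after dispatch inside the look-back: 62 if sent on 1 July, 63 to 92 if sent in June (17% to 25% of 365).
- The August-only secondary outcomes fall wholly inside the look-back.

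**3. Overlap if the look-back ends at extraction.** Any end date from 30 September 2021 to 31 July 2022 puts all 61 outcome days inside it. An end at 31 December 2021 does so. An end around mid-2022 also makes the look-back almost entirely post-dispatch.

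**4. Size of the shift.** The article gives no figure for lapsed children, so the following inputs are assumptions. Each practice has 85 children eligible before dispatch, 30% of them (25.5) with the outcome in both arms, so there is no effect among them. A further L lapsed children per practice enter through an overlap prescription at rate q, and a share s of these entrants have the outcome:

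uptake in an arm = (25.5 + s × L × q) / (85 + L × q)

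Difference, intervention minus control, in percentage points:

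| L | q, control v intervention | entrants per practice | s = 1 | s = 0.5 | s = 0 |
|---|---|---|---|---|---|
| 20 | 5% v 6.5% | 1.0 v 1.3 | +0.24 | +0.07 | -0.10 |
| 20 | 5% v 8% | 1.0 v 1.6 | +0.48 | +0.14 | -0.21 |
| 30 | 5% v 6.5% | 1.5 v 1.95 | +0.36 | +0.10 | -0.15 |
| 30 | 5% v 10% | 1.5 v 3.0 | +1.17 | +0.33 | -0.50 |

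For example, last row, s = 1: 28.5/88 - 27/86.5 = 32.39% - 31.21% = +1.17 points.

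The columns s = 1 and s = 0 are extremes. A child admitted by a July preventer is not automatically a success, because the outcome window opens on 1 August. A child admitted by a reliever may still receive a preventer by 30 September. With s = 0.30 the shift is exactly zero.

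**5. Break-even.** With no entrants in control and s = 1, the shift equals the planned half-width when the entrants, as a share of the 85, reach 0.0098/(0.70 - 0.0098) = 1.42%, or about 1.2 children per practice.

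**The case against.** Four points on the other side have weight.

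**The overlap is not stated.** A reader might infer that the article fixes the look-back at September 2020 to August 2021. It does not: 1 September 2021 grammatically dates age, and the 12 months are undated. The article is also a condensed account, and the protocol approved for the CPRD data may hold an index date. This stands as a limit on what can be asserted. It does not make the published rule safe, because neither date the article offers ends the look-back before dispatch. The practice criteria refer to the time of the intervention; the child criteria do not.

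**The inputs are assumed, and some are generous.** Entry at 8% or 10% against 5% is a relative increase of 60% or 100%. PLEASANT, which wrote to parents directly, found 30% in August, and TRAINS is one step further removed and advisory. At 5% v 6.5% every shift in the table is well inside the half-width. This stands.

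**It is not a false-positive mechanism.** A reader might infer that the rule inflates type I error. If the letter changes no prescribing at all, both arms select alike and the error rate is unaffected. Where the letter does act on lapsed children, part of the shift reflects real extra prescribing, which is the trial's aim. This stands. The estimate is still distorted, because untreated lapsed children are missing from the denominator.

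**The covariates help.** Adjusting for earlier preventer counts should absorb some of the difference in composition, and the table shows unadjusted risk differences while the planned estimate is an adjusted odds ratio. This stands in part: adjustment cannot restore children who are absent because nothing was prescribed.

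A reader might also infer that the letter prompts new asthma coding and so adds children by that route. The article describes a letter about reminding parents to continue preventers; nothing in it supports that inference.

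**Conclusion.** The concern holds in limited form. The rule that sets the primary denominator has an undated look-back. Read with the only date in the sentence, it includes about two post-dispatch months and 31 of 61 outcome days; read from extraction, it can include all 61. Arm can then influence who is analysed, and neither intention to treat nor the planned covariates fully repairs this.

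The bias is conditional on the letter changing prescribing in children without a recent prescription. Its size and sign cannot be derived from the article. The range of -0.50 to +1.17 points rests on assumed lapsed pools of 20 or 30 per practice, assumed entry rates, and extreme scoring of entrants; scoring half of them as successes reduces the two largest positive shifts to +0.14 and +0.33. A reader might infer an upward bias as large as the planned precision. That is possible under the most extreme assumptions shown, but it is not established. The point still matters because the trial is sized to estimate differences of about 1 point, and the data are described as still being cleaned before analysis.

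**What to change.** State the end of the look-back and place it before dispatch. Define the cohort as children with an asthma code already recorded and at least one asthma prescription in the 12 months ending the day before first dispatch (30 June 2021 or earlier). Keep age at 1 September 2021, which arm cannot affect. Use this denominator for the primary and all secondary outcomes.

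Report the published rule, with its end date made explicit, as a sensitivity analysis. Tabulate by arm the children admitted only under that rule and how many of them have the outcome, which replaces the assumptions above with observed counts.

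The cost is one sentence and a changed date filter on data already received. The article's amendment section lists changes to the patient population among those needing an amendment and approval; if the full protocol already ends the look-back before dispatch, a clarification is enough. A few newly treated children leave the primary denominator, so any effect on them appears only in the sensitivity analysis. Planned precision stays at 0.98 points if about 85 children per practice remain.

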### Data source

The data for this study will be routinely collected data extracted from the Clinical Practice Research Datalink—Aurum (CPRD Aurum) database. This database covers approximately 20% of the UK’s population, with over 1300 general practices participating [16]. CPRD Aurum is a database of de-identified patient data that can capture all medical contacts, from prescription requests to out-of-hours contacts, along with the reason for the contact. The data is contributed by general practices.

CPRD will extract data from primary care medical 6 months post-follow-up. The research team will receive all data fully anonymised and will not have access to any patient identifiable data.

### Allocation of preventer prescription

All medicines that have been prescribed will be reviewed, and identify all the asthma medications that have been prescribed. The asthma preventer prescription will be used to determine the primary outcome, whilst prescriptions for short-course oral steroids will be used to inform the definition of the secondary outcomes, including unscheduled care.

### Allocation of scheduled vs. unscheduled contacts

To ascertain whether a clinical contact was scheduled or unscheduled, we will use the contact codes used by the GP practice captured within the practice database. We are defining a scheduled contact as any contact that is part of the patient’s planned care, such as an asthma review, a medical review, repeat prescription, or immunisation. An unscheduled contact will be any contact not part of their care plan that is either patient initiated or as a result of illness. The decision (scheduled vs unscheduled) will be assisted by any prescription issues associated with the contact. For example, if there is a prescription for a short course of oral corticosteroids, this would infer both the contact is unscheduled, and it had a respiratory diagnosis. To ensure the allocation of scheduled and unscheduled contacts, we will draw on our experience of the coding for the PLEASANT study. Also, as part of the study team, we have a current GP to consult at each stage. In addition, the trial steering committee comprises two GPs and a practice nurse who also could advise us.

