## Glossary

Asthma: Asthma refers to a chronic inflammatory illness of the airways. Chronic inflammation is linked with airway hyper-responsiveness, resulting in recurrent episodes of symptoms such as tightness in the chest, breathlessness, wheezing, and coughing with different intensities over time [19].
Asthma preventer medication: A type of asthma treatment that is used to prevent and control asthmatic symptoms should be taken daily. In this trial, we are looking for when a child collects their or her asthma preventer medication during, and just after, the summer holidays (1 August 2021–30 September 2021).
Scheduled medical contact: A planned appointment for a child with asthma with the GP practice as part of their asthma care plan.
Unscheduled medical contact: An unplanned visit by a child with asthma to a GP practice or other health setting (e.g. hospital contacts, walk-in clinics)
Unscheduled medical contact: with a respiratory diagnosis: An unplanned visit by a child with asthma to a GP practice or other health setting (e.g. hospital contacts, walk-in clinics) for which there is a respiratory diagnosis

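### Scheduled contact is defined in two incompatible ways, and under the Methods definition the two pooled contact outcomes partly count the prescriptions the intervention aims to change

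*Protocol article*

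**What the plan says.** The section on allocating scheduled and unscheduled contacts defines a scheduled contact by its place in the patient's "planned care, such as an asthma review, a medical review, repeat prescription, or immunisation". The Data source section agrees with that broad reading: the database "can capture all medical contacts, from prescription requests to out-of-hours contacts, along with the reason for the contact".

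The Glossary gives a narrower definition of the same term: "A planned appointment for a child with asthma with the GP practice as part of their asthma care plan".

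Secondary outcome measures lists six contact outcomes for September to December 2021, each also by month:

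- unscheduled contacts (proportion and number);
- scheduled and unscheduled contacts pooled (proportion and total number);
- unscheduled contacts with a respiratory diagnosis (proportion and number).

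On prescribing, the primary objective is to "determine whether the intervention increases asthma prescription uptake in children with asthma in August and September". The primary outcome is the proportion of children "who have a prescription for an asthma preventer medication from 1 August 2021 to 30 September 2021". Secondary prescription outcomes include September alone and the six months from 1 July 2021. Nothing in the article removes prescription records from the contact outcomes or says which definition of scheduled contact governs.

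**The concern.** There are two linked problems. First, the definitions classify the same records differently, so the two pooled outcomes depend on which one the programmer follows. Second, under the broader definition a repeat preventer prescription issued in September can be a success in the primary outcome and also a medical contact. The pooled outcomes then mix the targeted behaviour with health-care use. A between-arm difference in them could reflect prescribing alone and be misread as a change in consultations.

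**Working it through.** **Step 1. The two definitions applied to the same records.**

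| Record, September to December | Methods definition | Glossary definition |
|---|---|---|
| Planned asthma review appointment | scheduled | scheduled |
| Repeat prescription, no appointment | scheduled | not scheduled |
| Immunisation outside the asthma care plan | scheduled | not scheduled |

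The definitions differ in two respects: any contact against an appointment, and planned care in general against the asthma care plan.

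**Step 2. Which outcomes are affected.** Scheduled records enter only the two pooled outcomes. The four unscheduled-contact outcomes do not count them, and the primary outcome counts prescriptions, not contacts.

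**Step 3. Overlap in time.** The contact window opens on 1 September. Overlap with the primary outcome (August and September) is therefore September only. Overlap with the six-month prescription outcome (from 1 July) is the whole of September to December. August prescriptions never enter the contact outcomes.

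**Step 4. The plan's own precision figure, for scale.** The Sample size section gives "approximately 1389 GP practices (694 on intervention and 695 on control"), "we also anticipate 85 school-age children having asthma per practice", and "Assuming an expected rate of 30% of people collecting their prescription and an intraclass correlation of 0.03".

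- Design effect: 1 + (85 − 1) × 0.03 = 3.52.
- Standard error of the difference: √[0.30 × 0.70 × 3.52 × (1/(694 × 85) + 1/(695 × 85))] = 0.00500.
- Half-width of the 95% interval: 1.96 × 0.00500 = 0.0098, or 0.98 points.

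This reproduces the stated 1%. The figure is correct, and the definitional problem does not depend on it.

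**Step 5. Size of the shift (illustration).** Suppose there is no true effect on clinical contacts, and that prescription-only contacts in the window differ between arms by d.

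- *Count outcome.* Each such record adds one contact, so the mean differs by exactly d.
- *Proportion outcome.* Let r be the control proportion with a prescription-only contact and c the probability of a clinical contact, independent of it. The proportion with any contact is 1 − (1 − c)(1 − r) in control and 1 − (1 − c)(1 − r − d) in intervention. The difference is (1 − c)·d, whatever r is.

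| d (points) | c = 0.3 | c = 0.5 | c = 0.7 |
|---|---|---|---|
| 1 | 0.7 | 0.5 | 0.3 |
| 2 | 1.4 | 1.0 | 0.6 |
| 4 | 2.8 | 2.0 | 1.2 |

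Negative d reverses the signs. Taking r = 0.30, and assuming that 85 children per practice and an intraclass correlation of 0.03 also hold for contacts, the half-width for the any-contact proportion is about 1.1, 1.0 and 0.9 points for the three values of c. A 1-point difference in prescribing would thus stay inside the half-width and a 4-point difference would exceed it. For reference, 4 points is the absolute August increase that the Background reports for PLEASANT; an August increase itself falls outside the contact window. With prescription-only records excluded, the shift is zero.

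**The case against.** Counting repeat-prescription contacts as planned primary-care activity is a legitimate measure of total workload. The section on allocating contacts does give an operational rule, and says that coding will draw on PLEASANT experience and GP advice. Whether a bare issue record counts is the kind of code-list detail that an article may leave to the full protocol. This argument has force against asking for a code list. It does not remove the conflict, because the article defines the term twice and incompatibly, and experience with coding does not say which definition governs.

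Three stronger readings are tempting, and the document does not support them.

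- *That the overlap hides or reverses the benefit seen in PLEASANT.* The Abstract speaks of medical contacts, but the Background describes the reduction as one in unscheduled contacts, and Secondary analysis names only unscheduled contacts. Those outcomes are untouched.
- *That a successful intervention must raise total contacts.* More September prescribing would raise them, but prescriptions brought forward from September into August would lower them.
- *That the artefact is as large as the stated precision.* This would need an arbitrary 1-point gain in September prescribing and a full one-for-one shift, which applies only to children with no other contact in the window. The 30% rate in the Sample size section is not tied to a month or window either, so a September share cannot be derived from it.

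**Conclusion.** The point holds for two secondary outcomes, the pooled proportion and the pooled total. Their content depends on which definition is used, and under the Methods definition they cannot be read as health-care use separate from prescribing. That conclusion rests on the text alone.

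The size is not known. The shifts in the table assume values for d and c, independence of prescription and clinical contacts, and no true effect on consultations. They show that the artefact could lie below or above the likely half-width, with either sign. Because the remedy is cheap and the contamination follows from a stated rule, this deserves correction and is more than a matter of missing detail.

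**What to change.** Reconcile the Methods section and the Glossary so that one definition of scheduled contact applies throughout, and state how immunisations are treated under it. Exclude prescription-issue-only records, meaning those with no consultation or review code, from the two pooled contact outcomes. Report the version that includes them as a sensitivity analysis, for comparability with PLEASANT.

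The cost is a change of wording, a code-list rule and one extra analysis. The small downside is that the main pooled figure becomes less directly comparable with PLEASANT, which the sensitivity analysis covers. Trial status says that the data are being processed and cleaned ahead of analysis, so at that stage the rule can still be set beforehand.
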